### Data monitoring

A Data Monitoring Committee (DMC) will not be established in this trial because there are no unusual high safety concerns related to our included trial participants. The treatments in this trial do not differ from the standard primary care accepted by the Swedish Association of Local Authorities and Regions and the risk of harm for trial participants is considered low. No interim analysis will be performed, and we do not plan to collect and report adverse events and other unintended effects. The recruitment of patients will be carefully monitored during the whole study by one of the study researchers (FG), who will be in contact with the study coordinators of each PCRU. If needed, measures will be taken and adjustments made to increase the speed of the recruitment rate. FG will also meet all the study coordinators each month to review the enrolment procedures of participants and the recruitment rate.

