### Setting

The study will be conducted at six primary care rehabilitation units (PCRUs) in Stockholm County Council, Sweden. If needed, additional units will be included. The operations manager for each PCRU has signed a written certificate to assure that they will provide sufficient resources to both carry out the study and guarantee the safety of the participants. The PCRUs are reimbursed through the Stockholm County Council. Twelve PCRUs in the Stockholm County Council were initially informed about the study by email and invited to participate. For each of the six PCRUs interested in participating, an information meeting was scheduled. Before the start of the study each PCRU was informed about the study methods in more detail and given the opportunity to give feedback on how to improve the efficiency in the recruitment of participants.

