### Study treatments

During the first (baseline) visit all participants will meet a chiropractor and/or a physiotherapist for an initial examination which includes diagnosis and the medical history of the patient. The participants are randomised to one of four treatment groups:
*Information and advice*: participants are given oral and written information on how to manage non-specific CLBP and advice about the importance of staying active and avoiding rest. Each participant is given a booklet with information on how to stay active [7, 29]
*Physiotherapy, and information and advice*: the treatment primarily involves training and exercise such as stabilisation training, functional training, mobility training and postural control [7]. The duration, number and content of the treatment is at the discretion of the physiotherapist. Participants are also given information, advice, and a booklet [29]
*Chiropractic care and information and advice*: the treatment primarily involves spinal manipulation defined as a high-velocity, low-amplitude movement at the limit of joint range that takes the joint beyond the passive range of movement [7]. The duration, number, and content of the treatment is at the discretion of the chiropractor. Participants are also given information, advice, and a booklet [29]
*Chiropractic care, physiotherapy, and information, and advice*: the treatment primarily involves a combination of spinal manipulation (defined as a high-velocity, low-amplitude movement at the limit of joint range that takes the joint beyond the passive range of movement) and training and exercise (e.g. stabilisation training, functional training, mobility training and postural control) [7]. The duration, number, and content of the treatment is at the discretion of the chiropractor and physiotherapist. Participants are also given information, advice, and a booklet [29]

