### Data collection

Data will be collected at baseline (after randomisation and before the treatment starts), and at follow-up, 3, 6, and 12 months after baseline. Each participant fills out a computer-based questionnaire at each measurement occasion. The day before each follow-up occasion, each participant is sent a reminder by email to fill out the questionnaire. If needed, a second and a third reminder is sent 2 and 7 days after the follow-up occasion. All data will be obtained from the computer-based questionnaire and from the chiropractor and/or physiotherapist reporting the number and content of treatments.

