## Discussion

In this pragmatic RCT we investigate the effectiveness and cost-effectiveness of chiropractic care and/or physiotherapy, when added to information and advice. The strengths of the trial include the use of a pragmatic RCT to reflect clinical practice, the conduct of an economic evaluation alongside a RCT, the use of standardised health outcome measures and a randomisation process with the researchers blinded for treatment group allocation, and the recruitment of large study population with a sufficient power to detect clinically important differences between groups.

A limitation of the study is the difficulty in blinding patients as to which treatment alternative they are allocated, which could lead to an expectation bias that may influence the results. An expectation bias may work in both directions depending on whether patient expectations and beliefs are positive (placebo effect) or negative (nocebo effect). We have not included any questions to measure patient expectations and beliefs before the treatment starts, which implies that we cannot estimate the potential expectation bias. On the other hand, which is a strength of the study, the results from our pragmatic RCT will reflect real effects for patients with CLBP in a primary care setting. Some patients do not always feel that they will get the treatment they would prefer, which may also affect the outcome of the treatment in clinical practice. Another limitation is the follow-up period in the trial, which is 1 year. Ideally, we would like to have a 2-year follow-up to be able to examine the effectiveness and cost-effectiveness of chiropractic care and physiotherapy in the long run.

CLBP is a severe public health problem associated with substantial costs for society. Although a wide range of treatment options exist for CLBP, the scientific basis to recommend the use of one treatment alternative over another is limited. The results from our study will improve the basis for health care decision-making and policy recommendations on how to use limited health care resources to improve health for people suffering from CLBP in Sweden. Our findings should be considered when producing and updating evidence-based guidelines and recommendations on which treatment strategies to use for CLBP.

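### Adverse events are deliberately left unrecorded, so identified or short-lived harms cannot be compared between arms, and low expected risk does not by itself justify this

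*Protocol article*

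**What the plan says.** The protocol article's Data monitoring section makes three linked statements:

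- on risk, "the risk of harm for trial participants is considered low", with the added reason that the treatments do not depart from accepted standard primary care;
- on oversight, "A Data Monitoring Committee (DMC) will not be established in this trial";
- on harms data, "we do not plan to collect and report adverse events and other unintended effects".

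Other sections bear on the same point:

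- **Study treatments.** In the chiropractic arm "the treatment primarily involves spinal manipulation defined as a high-velocity, low-amplitude movement at the limit of joint range"; the combined arm uses the same technique together with exercise. Number, duration and content are left to the provider.
- **Data collection.** "Each participant fills out a computer-based questionnaire at each measurement occasion". The only other source is data "from the chiropractor and/or physiotherapist reporting the number and content of treatments".
- **Setting.** Each unit's operations manager has certified in writing that there will be resources to run the study and "guarantee the safety of the participants".
- **Discussion.** "Our findings should be considered when producing and updating evidence-based guidelines and recommendations on which treatment strategies to use for CLBP". The Background has a similar sentence.

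**The concern.** The decision is stated outright, so it is not a detail that the article has left to a fuller protocol or analysis plan. No other section reverses it. The outcome, data collection and analysis sections contain no harms measure, and Data collection names only two data sources, neither of which asks about unintended effects.

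Low expected risk is a good reason for not convening a monitoring committee. Whether to record harms is a separate decision. The low-risk statement is a premise for which the article cites no data, and the trial is well placed to examine it because it has a randomised advice-only arm. By choosing not to record events, the trial gives up that comparison and leaves the premise untested. Readers who use the results for guidelines would see benefit and cost, with harm visible only as far as it shifts the outcome scores, work or resource use.

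**Working it through.** No figure in the plan needs reproducing, because the point concerns a decision. The check has two parts.

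**1. What the planned data can and cannot show about harm**

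| Planned measure (section) | Harm it can reflect | Harm it misses |
|---|---|---|
| ODI, self-rated health, EQ-5D-3L, working status (Outcome measurements) | Net worsening still present at 3, 6 or 12 months | Events resolved between forms; the cause of any worsening |
| NRS (Secondary outcome measures) | Pain at the moment of answering | Flares between forms |
| Medicines, visits, examinations, hospital days (Costs and QALYs; Follow-up) | Care used in the preceding 3 months | Events without care; the reason for care; months 7 to 9 |
| Provider report (Data collection) | None; it covers treatments given | All harms |

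The gap in the third row follows from the schedule. Forms at 3, 6 and 12 months with 3-month recall cover months 1–3, 4–6 and 10–12, so months 7–9 are not covered.

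**2. What collection would yield**

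Inputs from Required sample size and Randomisation: 600 participants in four groups of 150, with 20% dropout expected. Two of the four groups receive manipulation.

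- Randomised to manipulation: 2 × 150 = 300. After dropout: 300 × 0.8 = 240. The two arms without manipulation have the same numbers.
- Zero events, one-sided 95% upper bound: 1 − 0.05^(1/N).
  - N = 300: 0.99%
  - N = 240: 1.24%
- Chance of seeing at least one event at true risk p: 1 − (1 − p)^N.

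| True risk (assumed) | N = 300 | N = 240 |
|---|---|---|
| 1% | 95% | 91% |
| 0.5% | 78% | 70% |
| 0.1% | 26% | 21% |

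- Comparing common reactions, two-sided 5%, normal approximation, assumed rates of 10% and 20%, 240 per side (manipulation against no manipulation):
  - SE under no difference = √(2 × 0.15 × 0.85 / 240) = 0.0326
  - SE under the alternative = √((0.10 × 0.90 + 0.20 × 0.80) / 240) = 0.0323
  - z = (0.10 − 1.96 × 0.0326) / 0.0323 = 1.12, so power is about 0.87
- The same rates for one pair of arms (120 against 120) give power of 0.58.

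The event rates are my assumptions, as the document gives none. The calculations show that collection would inform on common reactions and would roughly exclude risks above 1%. It would not characterise rare events.

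**The case against.** The strongest reply is that this is a reasoned and disclosed choice. The trial is pragmatic, it has ethics approval, its treatments are ordinary primary care, and the section gives its reasons. There is no internal contradiction and no wrong figure. That is correct, so the point rests only on the choice being poorly supported by the reason given. I do not rely on what the cited reporting guidelines may require, since they are not at hand.

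A reader might also infer four stronger things that the document does not support:

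- **That the trial cannot weigh harm against benefit at all.** Lasting net harm does enter ODI, NRS, EQ-5D-3L and hence QALYs, and care-generating harm enters costs, in every arm including advice only. What is lost is identified and transient harm.
- **That the trial wants guidelines to adopt these treatments.** The research questions ask which treatment, if any, is cost-effective, and the Discussion asks only that findings be considered.
- **That participants' safety is unmonitored.** Unit managers have certified safety resources, clinicians examine participants and individualise care, and participants may withdraw at any time. What is absent is any described trial-level collection of safety information.
- **That one extra item would settle the safety question.** At a true risk of 0.1%, the chance of seeing even one event is only 21–26%.

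The objection also has force on how harms are asked about. An item limited to symptoms blamed on treatment would work poorly in the advice-only arm, where there is little treatment to blame. Provider reporting would be unequal because contact differs by arm. Both affect the remedy but do not remove the need for one.

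**Conclusion.** The point holds in limited form and is worth acting on. As written, the trial will hold no identified adverse events, cannot compare transient harms between arms, and cannot check its own low-risk premise. Absence of a monitoring committee is adequately justified; absence of any harms record is not.

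The realistic gain from a change is a comparison of common reactions and an upper bound of about 1.0% to 1.2% if no event is seen in the pooled manipulation arms. The bound assumes 300 randomised or 240 followed up, complete reporting among those followed, and a single risk across the two arms. Incomplete recall would make it optimistic.

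**What to change.** Amend the Data monitoring section to provide for collecting and reporting unintended effects, and then:

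- add one structured item to the existing 3-, 6- and 12-month questionnaires: new or worsened symptoms since the last questionnaire, whether care was sought, and seriousness;
- word it identically in all four arms, with no requirement that the participant attribute the symptom to treatment;
- set the recall period to the interval since the previous form, so that months 7–9 are covered;
- report the answers descriptively by arm as the main harms comparison;
- add an adverse-event field to the provider report as a supplement only, since provider contact differs by arm;
- notify the study lead of serious events.

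Both forms already exist, so the change is a minor amendment. Its costs are slight respondent burden, reporting bias in an open trial, and poor recall of brief reactions over three to six months. Trial status gives a recruitment start of 1 April 2017 and a protocol version 1 date of 9 July 2017. Participants enrolled before the amendment would have incomplete harms data, and the report should say how many.

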### Data collection

Data will be collected at baseline (after randomisation and before the treatment starts), and at follow-up, 3, 6, and 12 months after baseline. Each participant fills out a computer-based questionnaire at each measurement occasion. The day before each follow-up occasion, each participant is sent a reminder by email to fill out the questionnaire. If needed, a second and a third reminder is sent 2 and 7 days after the follow-up occasion. All data will be obtained from the computer-based questionnaire and from the chiropractor and/or physiotherapist reporting the number and content of treatments.

#### Baseline

Baseline data will be collected during the first visit or at 1–4 days before the first visit at the PCRU. Data on individual characteristics (age, sex, education, smoking status, physical activity, use of pain killers, and pain duration), outcome measures (back pain-related functional limitation, pain intensity, general health, HRQoL, working status) and resource consumption (pharmaceuticals, health care visits, clinical examinations, and hospital days) are collected.

#### Follow-up at 3, 6, and 12 months

At 3, 6, and 12 months after baseline data on outcome measures (back pain-related functional limitation, pain intensity, general health, HRQoL, working status) and resource consumption (pharmaceuticals, health care visits, clinical examinations, and hospital days) are collected. At each follow-up occasion (and at baseline) the participant is asked to recall their resource consumption during the last 3 months. Data on physical activity is also collected at follow-up.

### Timeline

The recruitment of patients started on 1 April 2017 and is expected to be finalised by 31 December 2019. All data for all follow-up occasions is expected to be collected by 31 December 2020. The data analysis, writing of scientific manuscripts and submissions to peer-reviewed scientific journals will be carried out during 2021 and 2022. A summary of the study outline is given in Fig. 2.

**Fig. 2 Fig2:**
[figure not shown]
Schedule of enrolment, interventions, and assessments

#### Required sample size

A change of 10 percentage points on the ODI scale is usually defined as the minimal clinically important difference (MCID) [45]. To detect a reduction of 10 percentage points (SD of 15) in the ODI score, which is in agreement with the study of Davidson et al. [45] and Hägg et al. [46], with a two-sided 5% significance level and a power of 80%, a sample size of 150 patients per group will be necessary, given an anticipated dropout rate of 20%. Each PCRU will recruit subjects until the required number is achieved. The enrolment period will extend over 33 months. The projected sample size will provide sufficient statistical power for linear mixed regression and Generalised Estimating Equation (GEE) models considering compound symmetry of the covariance structure and the number of repeated measures [47]. Further, a change of 10–30 percentage points in the NRS scale is usually defined as a MCID [48, 49]. To detect a reduction of 10 percentage points in the NRS, with a two-sided 5% significance level and a power of 80%, a sample size of 146 patients per group will be necessary, given an anticipated dropout rate of 20%.

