**Methods/design:**

This is a pragmatic randomised controlled trial, where participants are recruited through six primary care rehabilitation units (PCRUs) in Stockholm County Council, Sweden. Individuals with non-specific CLBP are individually randomised to one of four treatment groups: ‘information and advice’; ‘physiotherapy, and information and advice’; ‘chiropractic care, and information and advice’; or ‘chiropractic care, physiotherapy, and information and advice’. A sample size of 600 participants will be recruited during a period of 33 months. A computer-based questionnaire is used to collect data on back pain-related functional limitation (Oswestry Disability Index), pain intensity (Numeric Rating Scale), general health (self-rated health), health-related quality of life (EQ-5D-3L), and working status (measured as percentage of full-time work). Data will be collected at baseline, and at 3, 6, and 12 months after baseline.

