#### Primary outcome measure

The primary analysis is to evaluate between-group differences in percentage point change in ODI scores at 6 months compared to baseline. One-way analysis of variance (ANOVA) will be used to evaluate the between-group difference for the primary outcome variable ODI at 6 months. A Levine’s test will be employed to check the assumption of equality of variance for the ANOVA. Assumption of normality will be checked by using skewness and normal probability plot. In case of violation of the normality assumption, we will use the non-parametric Kruskal-Wallis H test which does not require the assumption of normality. If the assumption of homogeneity of variance is violated we will use, the Welch or the Brown and Forsythe test. If the overall ANOVA is significant, we will perform further analysis using a Tukey or Games-Howell post hoc pairwise comparison. We will use Games-Howell if there is a violation of the equality of variance assumption. To evaluate effect size, we will present the difference between means, 95% confidence interval and the partial eta-squared (*η*
^2^).

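### The 150 patients per group called necessary for the ODI do not follow from the stated 10 points, SD 15, 80% power and 20% dropout, which give 45–47 per group

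*Protocol article*

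**What the plan says.** The Required sample size section takes 10 percentage points on the 0–100 ODI scale as the minimal clinically important difference. It sets the target as "To detect a reduction of 10 percentage points (SD of 15) in the ODI score" and concludes that "with a two-sided 5% significance level and a power of 80%, a sample size of 150 patients per group will be necessary", with an anticipated dropout of 20%. The Abstract has participants "individually randomised to one of four treatment groups", and four groups of 150 make up the total: "A sample size of 600 participants will be recruited during a period of 33 months".

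The analysis that this number serves is in the Statistical analysis section, under Primary outcome measure: "One-way analysis of variance (ANOVA) will be used to evaluate the between-group difference for the primary outcome variable ODI at 6 months". If the ANOVA is significant, Tukey or Games-Howell pairwise comparisons follow.

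The sample size section mentions no adjusted alpha, design effect, correlation between measurements or subgroup allowance. It adds that the projected size will also be enough for linear mixed and GEE models, but does not say that 150 was derived from those models.

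**The concern.** The sentence gives every input that a two-group comparison of means needs: difference, SD, alpha, sidedness, power and dropout. A reader can therefore recompute the result, and it comes out at about a third of the stated figure. A standardised difference of 10/15 = 0.67 is large, and 120 evaluable patients per group is far more than 80% power requires.

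At stake is what the trial was designed to detect. Either one of the inputs is not the one used, or the power and detectable difference that go with 150 per group are misreported. The calculation is the stated ODI justification for 600 patients over 33 months, and it fixes the 10-point benchmark against which the primary result will be read.

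**Working it through.** **Inputs** (all from Required sample size unless noted)
- Difference δ = 10 ODI points; SD σ = 15
- Two-sided α = 0.05; power 80%
- Dropout 20%, so recruited n = evaluable n / 0.8
- Stated result: 150 per group, i.e. 150 × 0.8 = 120 evaluable
- Four groups (Abstract); one-way ANOVA, then Tukey or Games-Howell (Primary outcome measure, Statistical analysis)

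**1. Reproducing the plan's figure**

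Normal approximation: n = 2(z₀.₉₇₅ + z₀.₈₀)² (σ/δ)² = 2 × (1.960 + 0.8416)² × (1.5)² = 2 × 7.849 × 2.25 = 35.3, so 36 evaluable. Recruited: 36/0.8 = 45.

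Two-sample t-test: 36.3, so 37 evaluable. Recruited: 37/0.8 = 46.25, so 47.

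The stated 150 is 150/47 = 3.2 to 150/45 = 3.3 times as large. It is not reproduced.

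**2. Readings closer to the planned analysis** (δ = 10, σ = 15, 80% power)

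| Reading | Evaluable per group | Recruited per group |
|---|---|---|
| Four-group F-test, means 0, 0, 10, 10 | 26 | 33 |
| Four-group F-test, means 0, 5, 5, 10 (least favourable pattern with a 10-point range) | 51 | 64 |
| Tukey pairwise, four groups | 53–54 | 67–68 |
| Bonferroni, six pairs, t-test | 57 | 72 |

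The Bonferroni row by normal approximation: 2 × (2.638 + 0.8416)² × 2.25 = 54.5, so 55; the t-test gives 56.3, so 57, and 57/0.8 = 71.25, so 72.

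With the stated SD and power, the largest of these is 72, which is 48% of 150. A rank test at its worst-case efficiency of 0.864 gives 53 recruited, and a 10-point 2×2 interaction gives 89. Raising power to 90% with Bonferroni for six pairs gives 89.

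**3. What 120 evaluable per group delivers**

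Standard error of a difference: 15 × √(2/120) = 1.936.

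- Power for 10 points: 10/1.936 = 5.164; Φ(5.164 − 1.960) = 0.999
- Power at α = 0.05/6: Φ(5.164 − 2.638) = 0.994
- Difference detectable with 80% power, unadjusted: (1.960 + 0.8416) × 1.936 = 5.4 points
- The same at the Tukey critical value (2.578): (2.578 + 0.8416) × 1.936 = 6.6 points

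**4. What would make 150 correct**

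- Keeping 10 points and 80% power: σ = 10 / [2.8016 × √(2/120)] = 27.6, against the stated 15
- Keeping SD 15 and 80% power: a difference of about 5.4 points, against the stated 10
- Other combinations also come close, such as SD 21.2 (change scores with no correlation between visits) at 90% power with Bonferroni for three comparisons, which gives 153. None of these inputs is stated.

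**The case against.** The best defence is that the ODI need not be the only driver of the sample size. The same section gives a separate NRS requirement, "a sample size of 146 patients per group will be necessary", close to 150, and refers to mixed and GEE models with a citation that cannot be examined here. The discrepancy is also in the safe direction. Both observations stand. They do not repair the ODI sentence, which attributes 150 to the ODI inputs alone, but they limit what follows from it. Four stronger readings are tempting and are not supported.

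- **The trial is two to three times too large.** On the ODI inputs alone, 600 exceeds the need. With the NRS figure and the model-based remark in the same section, the document does not establish that 600 is excessive overall.
- **The NRS figure of 146 is also wrong.** No SD is given for it, so it cannot be checked. An SD left out of a condensed article is not evidence of an error.
- **The Discussion's power claim is false.** It describes "the recruitment of large study population with a sufficient power to detect clinically important differences between groups". On the stated inputs this is true, at 99.9% for 10 points. It would come into doubt only if the SD were much larger than 15, and nothing in the document shows that.
- **The trial was really sized for something smaller than 10 points.** The section says the opposite, and an SD near 27.6 would explain 150 just as well.

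Nor is it a defect in itself that differences below 10 points could reach significance; that happens in any large trial.

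**Conclusion.** The concern holds as an inconsistency in the ODI sample size sentence. The stated inputs need 45–47 recruited per group, and at most about 72 under the planned ANOVA, Tukey or six-way Bonferroni comparisons, not 150. With 150 randomised, power for 10 points is about 99.9% (99.4% at α = 0.05/6), and the 80%-power difference is about 5.4 points (6.6 with Tukey).

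This rests on reading SD 15 as the SD of the analysed outcome, equal allocation, and 20% dropout applied as n/0.8. Dropout applied as n × 1.2 gives 44–45 and does not alter the conclusion.

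The error is conservative. It leaves the planned tests intact and does not show under-powering on the stated inputs. It is a reporting correction that should be made, not a threat to the primary conclusion. Which input is wrong cannot be told from the document.

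**What to change.** Reconcile the inputs with the sample size in the Required sample size section, in one of two ways:

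1. If 10 points and SD 15 are the intended inputs, replace the claim of necessity with a statement of what the design delivers. Suggested text: *With 150 randomised (120 evaluable after 20% dropout) per group, the trial has over 99% power at two-sided 5% for a between-group difference of 10 ODI points at SD 15, and 80% power for a difference of about 5.4 points (6.6 points at the Tukey critical value).*
2. If 150 came from a larger SD, a smaller target difference, a higher power or an adjustment that is not mentioned, state that value in place of the current one and show that it yields 150.

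The authors must choose, because only they know the basis. The cost is a few sentences in the protocol or SAP. Recruitment and the planned analysis do not change. The correction is best made before the outcome data are analysed, so that the design target is on record before the results are interpreted.
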